#### Exploratory secondary analyses

2.10.2

Participation rates in exploratory subgroup analyses will be studied in the same manner as the primary endpoint. The same margin of non-inferiority will be used. There is no provision for alpha risk adjustment for these analyses. The different subgroups are: (i) women aged 50 to 59/60 to 69/70 to 74 years at baseline, (ii) beneficiaries/not beneficiaries of the Complementary Solidarity Health at baseline, (iii) women who consulted/did not consult at least one GP, gynecologist or midwife (during the follow-up period for women who did not have a bilateral mammogram during the 18 months, or from baseline until the date of the bilateral mammogram for women who had the screening) (iv) women residing in a municipality with a low deprivation index (per quintile of the deprivation index) (41).

Predictors of OS use will be assessed using a multivariate generalized mixed model fitted to the physician as a random effect, and as fixed effects: (i) the number of visits to the treating physician, GP, gynecologist, or midwife in the 18 months prior to enrolment, and from baseline to bilateral mammography or to the end of the follow-up period for women who did not have bilateral mammography, (ii) the woman’s age at baseline, (iii) the presence of a chronic condition measured *via* chronic drug use and testing, (iv) previous participation in OS.

A stepwise algorithm based on the Akaike information criterion (AIC) will be implemented to select variables that provide meaningful information independent of the main factors.

SMDM quality will be measured using the DCS and SDM-Q9 scales, responses to participation intent and knowledge of women about the OS. It will be compared between groups using a Student superiority test.

The care pathway of the women responding to the questionnaires will be studied and in particular the concordance between patients’ intention and effective participation in BC screening.

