#### Main criterion

2.10.1

The percentage of women having undergone BC screening, 18 months after the intervention, will be compared between the arms using a generalized linear mixed model, to adjust the analysis for the random effect of the practice.

A two-sided 95% confidence interval of the difference in participation rates between the two arms will be calculated. The lower bound of this confidence interval will be compared to the non-inferiority margin. Non-inferiority will be demonstrated if the lower bound of the confidence interval is greater than the margin of non-inferiority defined at 2%, on the Intention to Treat (ITT) population and Per-Protocol population. If non-inferiority is demonstrated and if the participation rate in the intervention arm is higher than the participation rate in the control arm, the hypothesis will be verified with a superiority test (bilateral at 5%, according to the same model as that of the non-inferiority analysis) (40). If the test is significant, it will be concluded that the participation rate in the intervention arm is significantly higher than the participation rate in the control arm.

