#### Main study sample

2.11.1

Based on a participation rate in 2020 of 49% for the five participating departments (11) assuming a margin of non-inferiority of 2 points to demonstrate that participation is non-inferior in the intervention arm, and considering a power of 80% and a bilateral alpha risk of 5%, the number of women to be included is equal to 9,808 in each arm, being a total of 19,616 women.

There are 2,847 GPs in the five departments (42). Considering that GPs operate from 1,570 different practices (42) the number of women targeted per practice will be 48. With an average cluster size of 48 women and an intraclass coefficient of 5%, the number of subjects to be included to account for this cluster randomization must be multiplied by 3.35, or 65,647 women (32,824 per group).

The number of GPs included will be approximately 2,847 in the five departments. The recruitment potential is approximately 25,000 women per month (personal communication from the CRCDC). The inclusion will therefore be done over 3 consecutive months.

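### Each exploratory subgroup is judged against the 2-point non-inferiority margin, a rule that has low power in small subgroups and cannot show whether the effect differs between them

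*Protocol article*

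**What the plan says.** Section 2.10.2 (Exploratory secondary analyses) states: "Participation rates in exploratory subgroup analyses will be studied in the same manner as the primary endpoint". It continues: "The same margin of non-inferiority will be used. There is no provision for alpha risk adjustment for these analyses".

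The manner referred to is set in section 2.10.1 (Main criterion). The lower limit of a two-sided 95% confidence interval for the difference in participation is compared with the 2-point margin, "on the Intention to Treat (ITT) population and Per-Protocol population", and a superiority test may follow. I read the margin as a loss of 2 points.

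The subgroups are:

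- age: "women aged 50 to 59/60 to 69/70 to 74 years at baseline"
- supplementary insurance: "beneficiaries/not beneficiaries of the Complementary Solidarity Health at baseline"
- consultation: "women who consulted/did not consult at least one GP, gynecologist or midwife"
- deprivation: "women residing in a municipality with a low deprivation index (per quintile of the deprivation index")

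If the last item means all five quintiles, that makes 3 + 2 + 2 + 5 = 12 subgroups. No arm-by-subgroup interaction is named. The predictor model in the same section lists neither arm nor an interaction among its fixed effects.

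**The concern.** The margin and the sample size belong together only for the whole sample. A subgroup holding a fifth or a tenth of the women has a much wider interval, so it can miss the margin even when the intervention changes nothing. The pass or miss then depends largely on subgroup size.

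Separate decisions also do not answer the question that readers bring to subgroups, which is whether the effect differs between them. One subgroup meeting the margin while another misses it is not evidence of a difference. That needs a direct contrast of the two effects.

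The stake is interpretation. Section 2.8.2.1 motivates the age and socio-economic breakdowns by social inequalities in screening, and section 3.1 notes a lack of evidence on decision aids among women who participate less. A report that non-inferiority was not shown in deprived women could be read as harm to equity when it reflects only imprecision.

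**Working it through.** **Inputs from the protocol article.** Participation 49%, margin 2 points ("assuming a margin of non-inferiority of 2 points to demonstrate that participation is non-inferior in the intervention arm"), 80% power, two-sided alpha 5%, 48 women per practice, intraclass correlation 0.05, and 65,647 women in total (section 2.11.1). Section 2.12 speaks of 75,000 women included.

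**Assumed.** A true difference of 0, equal arms, and subgroup shares f of 10% and 20%. The article gives no shares.

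**The plan's own figures.** Women per arm before inflation: 2 × 0.49 × 0.51 × (1.960 + 0.842)² / 0.02², which rounds up to 9,808, as stated. Design effect: 1 + 47 × 0.05 = 3.35, as stated. 19,616 × 3.35 = 65,714 against 65,647 stated, a gap of 0.1% that does not matter here. Whole-sample power at 65,647: the standard error (SE) is 0.714 points and Φ(2/0.714 − 1.96) = 80%. At 75,000 it is 85%.

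**Power within a subgroup of share f among N women.**

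- SE = √[2 × 0.49 × 0.51 × DE / (fN/2)]
- Power = Φ(0.02/SE − 1.96)
- If the subgroup follows whole practices, DE = 3.35.
- If it is spread evenly over practices, DE = 1 + (48f − 1) × 0.05. That is 1.43 for f = 20% and 1.19 for f = 10%.

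Example, f = 20% and N = 65,647, so fN/2 = 6,565 per arm. Spread: SE = √(0.4998 × 1.43/6,565) = 1.043 points, power Φ(1.917 − 1.96) = 48%. Whole practices: SE = 1.597 points, power Φ(1.252 − 1.96) = 24%.

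| Share | N | Power, whole practices | Power, spread | 95% CI half-width (points), spread to whole practices |
|---|---|---|---|---|
| 20% | 65,647 | 24% | 48% | 2.05 to 3.13 |
| 20% | 75,000 | 27% | 54% | 1.91 to 2.93 |
| 10% | 65,647 | 14% | 32% | 2.64 to 4.43 |
| 10% | 75,000 | 16% | 36% | 2.47 to 4.14 |

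Deprivation is measured by municipality of residence, so the quintiles probably cluster with practices, which moves power towards the lower figures. Requiring both analysis populations to meet the margin can only lower power further. Large subgroups are much less affected: a 90% share spread over practices keeps 79% power at 65,647 women and 84% at 75,000.

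**All five deprivation quintiles meeting the margin, 20% each.**

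- Whole practices: the quintiles are independent. 0.240⁵ = 0.08% at 65,647 and 0.267⁵ = 0.14% at 75,000.
- Spread: every practice contributes to all five quintiles, so the estimates share the practice effect. With about 9.6 women per practice per quintile, their correlation is 0.05/(0.05 + 0.95/9.6) = 0.34. The joint normal probability with that correlation is about 10% at 65,647 and 14% at 75,000.

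The range is therefore about 0.1% to 14%.

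**A mixed result.** At 75,000 women with whole-practice quintiles, the chance that some quintiles pass and others miss under no effect is 1 − 0.267⁵ − 0.733⁵ = 1 − 0.001 − 0.211 = 79%.

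**The case against.** These analyses are labelled exploratory in both the heading and the text, and the absence of alpha adjustment is declared openly. The primary method yields a difference with a confidence interval, so imprecision would be visible. The stated objective concerns predictors of screening use and participation by age and socio-economic level, not effect heterogeneity. An interaction test is the kind of detail a full analysis plan may hold, and that plan is not shown. Much of this stands: it limits the consequence, and the missing alpha adjustment is not the fault. It does not remove the point, because the article states positively that the primary rule and its margin apply in each subgroup. The exploratory label excuses multiplicity, but it does not make a pass-or-miss rule informative about differences.

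Three stronger readings are not supported.

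- A reader might infer that most small subgroups would fail. At 75,000 women, a 20% subgroup spread over practices is slightly more likely to pass than miss (54%), and all shares are assumed. The article does not say that the quintiles are quintiles of the study population.
- A reader might put the best-case chance that all five quintiles pass at about 4%, from 0.535⁵. That treats the quintiles as independent and ignores the practices they share in that case.
- A reader might conclude that no interaction analysis exists. The article names none, which does not show that none is planned.

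**Conclusion.** The point holds as a minor one. The article fixes a subgroup rule that has low power where subgroups are small and that cannot show whether the effect differs. If the true difference is 0, a 20% subgroup would meet the margin about 24–54% of the time and a 10% subgroup about 14–36%, across both sample sizes and both extremes of clustering. These figures rest on the article's 49% and 5%, on a cluster size of 48, and on assumed shares. They concern a missed margin in exploratory analyses. Nothing here touches the primary non-inferiority conclusion, and no decision in the article depends on a subgroup result.

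**What to change.** Change the wording of section 2.10.2.

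1. For the three baseline factors (age band, Complementary Solidarity Health, deprivation quintile), fit one mixed model per factor with arm, subgroup, arm-by-subgroup interaction and a practice random effect.
2. Report the risk difference with its 95% confidence interval in each level, and an interaction test on the risk-difference scale. A test on the logit scale can disagree with the differences reported.
3. State that no non-inferiority conclusion is drawn within subgroups.
4. Report the consultation subgroup descriptively only. It is defined after the intervention, over a window that ends at the mammogram for screened women, and section 2.6 has the intervention itself encourage consultation. An interaction on it could not be read as effect modification.

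The cost is wording only; no further data are needed. The trial gives up subgroup-level non-inferiority claims, for which it was not sized. Three unadjusted interaction tests at 5% carry a chance of about 1 − 0.95³ = 14% of at least one false signal, if treated as independent, so the exploratory label should stay.

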### Intervention and control procedures

2.6

One intervention arm and one control arm are planned.

In the “Decision aid for organized cancer screening” group (intervention arm), the intervention will combine sending letters to women and their GP. Women will receive their invitation to have a mammogram accompanied by a flyer mentioning the existence of the DA and encouraging them to consult their GP to make a shared decision. Physicians will receive a letter informing them of the correspondence their patients have received, the existence of the DA, a presentation of the different stages of SMDM and an incentive for their implementation.

In the “Standard organized cancer screening” group (control arm), the intervention will be limited to sending invitation letters, corresponding to the national standard (9).

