#### Primary objective and primary endpoint

2.8.1

The main part of this study is to assess whether sending information to women and GPs mentioning the existence of DAs and encouraging SMDM implementation along with the screening information letter (intervention arm) affects participation rate in BC OS, compared to only sending the invitation letter to eligible women (control arm) (see **Supplementary Material 1**).

The primary outcome is the participation rate in BC OS, in each arm during the 18 months following the invitation being sent. This duration takes into account the waiting times observed to benefit from screening mammography (see **Supplementary Material 1**).

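### Subgroup (iii) and the post-baseline visit count use an observation window that the outcome itself sets, so non-participants accumulate more visits by construction

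*Protocol article*

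**What the plan says.** The primary outcome (section 2.8.1) is participation in organized screening "in each arm during the 18 months following the invitation being sent".

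Section 2.10.2 then uses consultation after baseline in two places.

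- **Subgroup (iii)** splits women by whether they saw at least one GP, gynecologist or midwife. The window is "during the follow-up period for women who did not have a bilateral mammogram during the 18 months, or from baseline until the date"; for a screened woman, that end point is the day of her mammogram. The subgroups are analysed like the primary endpoint, and "The same margin of non-inferiority will be used".
- **Predictor (i)** of the mixed model for screening use combines two visit counts. One is taken "in the 18 months prior to enrolment", a fixed period that is the same for every woman. The other runs "from baseline to bilateral mammography or to the end of the follow-up period for women who did not have bilateral mammography".

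The section gives no offset, visit rate, landmark or time-varying treatment for the unequal windows. Section 2.6 says that the flyer in the intervention arm reaches women with the aim of "encouraging them to consult their GP to make a shared decision".

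**The concern.** A screened woman stops accruing visits on the day of her mammogram. An unscreened woman goes on accruing them for 18 months. The covariate is therefore partly a record of the outcome. If visits and screening are unrelated, non-participants will still show more visits, and more of them will be classed as having consulted.

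Two results are exposed.

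1. **The predictor coefficient.** The unequal windows push it downward. They can mask or reverse a true positive association between medical follow-up and screening. Predictors of screening use are a named secondary objective, and section 2.8.2.1 lists irregular medical follow-up among the factors of interest. The bias does not shrink with more data, so in a trial of this size it would look precise.
2. **The arm comparison in subgroup (iii).** Consultation status arises after randomization and is something the intervention tries to change. Consulters in one arm are then not exchangeable with consulters in the other, so the comparison is no longer randomized, yet it is to be judged against the 2-point margin.

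**Working it through.** **Inputs from the protocol.** Participation 49% and margin 2 points (section 2.11.1); follow-up 18 months (section 2.8.1); the windows quoted above. The plan states no figure for this point. As a check on the two numerical inputs, they reproduce the plan's size before cluster inflation: 2 × 0.49 × 0.51 × (1.960 + 0.842)² / 0.02² = 9,808 per arm, as stated.

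**Assumptions not in the protocol.** Visits follow a Poisson process at rate r = 0.1 to 0.3 per month, unrelated to screening. The wait to mammogram among participants is either exponential with mean 4 months, truncated at 18, or uniform over 0 to 18 months.

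**Step 1: probability of being classed as consulted.**

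- Non-participants: b = 1 − exp(−18r). At r = 0.2, b = 0.973.
- Participants, exponential wait with μ = 1/4: a = 1 − [μ/(μ + r)] × [1 − exp(−18(μ + r))] / [1 − exp(−18μ)]. At r = 0.2, a = 1 − 0.5556 × 0.9997 / 0.9889 = 0.438.
- Participants, uniform wait: a = 1 − [1 − exp(−18r)] / (18r). At r = 0.2, a = 1 − 0.9727 / 3.6 = 0.730.

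**Step 2: apparent participation at r = 0.2.** Consulters: 0.49a / (0.49a + 0.51b). Non-consulters: 0.49(1 − a) / [0.49(1 − a) + 0.51(1 − b)].

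- Exponential wait: 0.2148 / (0.2148 + 0.4961) = 30.2% in consulters; 0.2752 / (0.2752 + 0.0139) = 95.2% in non-consulters.
- Uniform wait: 0.3576 / (0.3576 + 0.4961) = 41.9% in consulters; 0.1324 / (0.1324 + 0.0139) = 90.5% in non-consulters.

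The true figure is 49% in every cell.

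**Step 3: odds ratio per visit.** Logistic regression of participation on the visit count alone, in 1,000,000 simulated women per row:

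| Visits per month | Planned window, exponential wait | Planned window, uniform wait | Same 18 months for all |
|---|---|---|---|
| 0.1 | 0.239 | 0.535 | 1.00 |
| 0.2 | 0.290 | 0.571 | 1.00 |
| 0.3 | 0.339 | 0.604 | 1.00 |

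The size depends on the assumed wait and visit rate. The direction does not.

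**Step 4: arm difference within subgroup (iii), with no effect on participation.** Keep 49% in both arms, multiply r by 1.1 or 1.2 in the intervention arm, and take the difference of the Step 2 formulas, in points:

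| r in control | Wait | Consulters, ×1.1 / ×1.2 | Non-consulters, ×1.1 / ×1.2 |
|---|---|---|---|
| 0.1 | exponential | +0.68 / +1.34 | +2.26 / +4.31 |
| 0.2 | exponential | +0.95 / +1.82 | +1.26 / +2.21 |
| 0.3 | exponential | +0.93 / +1.76 | +0.39 / +0.63 |
| 0.1 | uniform | +0.46 / +0.90 | +2.24 / +4.40 |
| 0.2 | uniform | +0.53 / +1.01 | +2.11 / +3.81 |
| 0.3 | uniform | +0.45 / +0.83 | +0.88 / +1.46 |

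With the same visit rate and timing in both arms, the difference is exactly 0.

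A delay can also produce a difference. With one visit per year and the wait uniform over 0 to 12 months (mean 6) in control, moving the mean to 7 months in the intervention arm gives +2.36 points in consulters and −1.37 in non-consulters. The bias can therefore take either sign.

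**The case against.** **The window has a reason.** Stopping at the mammogram leaves out visits that follow from it, such as those to discuss the result, which cannot have influenced participation. This stands as a rationale. It does not remove the unequal exposure, and a time-varying or landmark analysis leaves out the same visits without creating it.

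**The analyses are labelled exploratory.** This limits the consequence, since the primary conclusion does not depend on them. The label excuses imprecision and the absence of multiplicity control. It does not excuse a covariate whose measurement period is set by the outcome.

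**The size is uncertain.** This stands. Visit rate, waiting time and any uplift in consultation are assumptions. The check uses a single covariate, whereas the planned model has others. The protocol notes that the 18 months allow for observed waiting times, which gives no particular support to a short wait. The results are shown as ranges for this reason.

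**Stronger readings that the protocol does not support.** A reader might infer that subgroup (iii) would show an arm difference even if the intervention did nothing at all. It would not: the window rule applies alike in both arms, and with equal consultation and timing the artefact is zero. A reader might also infer that all of section 2.10.2 is compromised. It is not: subgroups (i) and (ii) are fixed at baseline, subgroup (iv) rests on municipality of residence, and the age, chronic-condition, previous-participation and pre-enrolment visit terms do not use this window. Nor does it follow that the fitted model must show visits lowering participation. A true positive association may offset the bias in part or in full, so the net sign cannot be predicted.

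**Conclusion.** The concern holds for subgroup (iii) and for the post-baseline part of predictor (i), and for nothing else. The primary analysis and the sample size are untouched.

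For the predictor, the fault is built into the definition. Under visits unrelated to screening, the unadjusted odds ratio per visit is about 0.24 to 0.34 with the 4-month wait and 0.53 to 0.60 with the uniform wait, instead of 1.0.

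For the arm comparison in subgroup (iii), the loss of randomization is certain in principle, but the numerical bias is conditional. A 10 to 20% rise in visits with no effect on participation gives about +0.45 to +1.8 points in consulters and +0.4 to +4.4 in non-consulters, against a margin of 2. The protocol gives no size for any such rise; it says only that the flyer encourages consultation. The definition should be changed before analysis.

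**What to change.** 1. Define subgroup (iii) by at least one visit to a GP, gynecologist or midwife in the 18 months before baseline.
2. In the predictor model, keep the pre-enrolment visit count and delete the post-baseline count.
3. If consultation after the invitation is of interest, analyse it separately, with visits as a time-varying covariate in a discrete-time or Cox model that accounts for practice clustering, or from a landmark date. Report it as descriptive and do not judge it against the 2-point margin.

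A fixed 18-month count after baseline would remove the difference in window length but would bring back visits made after the mammogram, so it is not the preferred remedy.

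The cost is wording in the protocol or analysis plan. Section 2.8.2.1 already provides for collecting consultations over 18 months before and after the intervention. The downside is that subgroup (iii) would then describe prior use of care rather than use after the invitation; item 3 covers that question.

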### Setting

2.2

In France, all patients over the age of 16 must follow a coordinated care pathway. General practitioners (GP) are at the center of this system. They coordinate access to care and specialists, are involved in screening and must be consulted as a priority. The GP system is based on a reciprocal choice: that of the patient and that of the GP.

The study is based on the regular GP/patient pair to measure the effect of the intervention. A cluster is defined as a group of GPs within the same primary practice address.

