### Randomization

2.5

GPs will be clustered within practices to avoid contamination bias stemming from shared tracking mechanisms and communication among GPs within a practice. As a result, two GPs working in a given practice will be assigned to the same study arm. The women will then be allocated to the same arm as their GP.

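### The exploratory predictors-of-use model names the physician as its random effect although the trial is clustered by practice: a real but minor inconsistency, with little effect on the predictors listed

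*Protocol article*

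**What the plan says.** Four parts of the protocol article put the clustering at the practice.

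- Section 2.2 (Setting): "A cluster is defined as a group of GPs within the same primary practice address".
- Section 2.5 (Randomization): "two GPs working in a given practice will be assigned to the same study arm". The reason given is that "GPs will be clustered within practices to avoid contamination bias stemming from shared tracking mechanisms and communication among GPs within a practice".
- Section 2.10.1 (Main criterion): the primary comparison uses a "generalized linear mixed model, to adjust the analysis for the random effect of the practice".
- Section 2.11.1 (Main study sample): the sample size is inflated for 48 women per practice and an intraclass coefficient of 5%.

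Section 2.10.2 (Exploratory secondary analyses) describes the predictors model differently, as a "multivariate generalized mixed model fitted to the physician as a random effect". It names no practice effect. The fixed effects listed are the number of visits before and after enrolment, "the woman’s age at baseline", "the presence of a chronic condition measured" through drug use and testing, and earlier participation in organised screening. A stepwise selection on the AIC follows. Neither the arm nor any other practice-level covariate is listed.

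**The concern.** A model with a physician effect and nothing above it takes women of two GPs in the same practice to be independent once the fixed effects are accounted for. The protocol's own reasoning says otherwise: it randomises by practice because GPs there share systems and talk to one another, and it sizes the trial on a practice-level correlation. With almost two GPs per practice on average, the omitted level is not empty.

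What is at stake is the precision reported for the first secondary objective. Omitting a higher level of clustering can make standard errors too small, most of all for covariates that women of one practice share. The AIC in the stepwise step is computed from the same likelihood, so it rests on the same independence assumption; no calculation was made of how far selection would change.

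**Working it through.** **Inputs.** From section 2.11.1: 2,847 GPs, 1,570 practices, 48 women per practice, intraclass coefficient 0.05, participation 49%, margin 2 points, power 80%, two-sided alpha 5%. From section 2.12: 75,000 women.

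**The plan's own figures first.**

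- Per arm before clustering: (1.96 + 0.8416)² × 2 × 0.49 × 0.51 / 0.02² = 9,808 after rounding up, as stated.
- Design effect: 1 + (48 − 1) × 0.05 = 3.35, as stated.
- Total: 19,616 × 3.35 = 65,714, against 65,647 stated, a difference of 0.1%.

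So the 5% coefficient is used for women sharing a practice, not only for those sharing a GP.

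**Size of the two levels.** 2,847 / 1,570 = 1.81 GPs per practice. 75,000 / 2,847 = 26.3 women per GP; 48 / 1.81 = 26.5 from the planned cluster size.

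**Covariate constant within practice, equal sizes, all correlation at practice level.** The physician-only model inflates the variance by 1 + 25.5 × 0.05 = 2.275. The true inflation is 1 + 47 × 0.05 = 3.35. Reported over true standard error: √(2.275 / 3.35) = 0.82, so the true one is 1 / 0.82 ≈ 1.2 times the reported one. The nominal 5% test then has a type I error of about 11%.

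**Unequal practice sizes and other covariates.** A generalised least squares calculation on the linear scale took 1,570 practices with a skewed assumed size distribution (mean 1.80 GPs, 55% with a single GP) and 26 women per GP. The fitted model had a physician effect only, with variance equal to the sum of the practice and GP variances. The truth had a practice effect, with or without a GP effect. The table gives true standard error / reported standard error under four assumed splits of the intraclass coefficient (practice / GP).

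| Covariate | 0.05 / 0 | 0.05 / 0.02 | 0.025 / 0.025 | 0.10 / 0 |
|---|---|---|---|---|
| Woman-level, not clustered | 1.00 | 1.00 | 1.00 | 1.00 |
| 5% of its variance between practices | 1.01 | 1.01 | 1.01 | 1.01 |
| 10% between practices | 1.02 | 1.01 | 1.01 | 1.02 |
| 20% between practices | 1.04 | 1.03 | 1.02 | 1.04 |
| Constant within practice | 1.37 | 1.32 | 1.22 | 1.44 |

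With a ratio r the true type I error is 2 × [1 − Φ(1.96 / r)]. This gives 5.0% to 6.0% for the first four rows and 11% to 17% for the last.

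A separate linear-scale simulation (400 practices, 1 + Poisson(0.81) GPs each, 26 women per GP, 1,500 replicates) gave reported / true ratios of 0.95 to 0.97 for covariates with a practice-level intraclass coefficient of 0.02 to 0.30. For a practice-level covariate it gave 0.74, that is 1 / 0.74 = 1.35. Taken together, the understatement is about 0 to 5% for woman-level predictors.

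**The case against.** The strongest reply is that the mismatch has almost no consequence for the model as listed. Every named fixed effect varies mainly between women of the same GP, and the physician effect absorbs most of the practice variance. That stands. A reader might infer that the model's standard errors are too small in general and its confidence intervals misleading; the calculations do not support that for the listed predictors.

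A second reply is that the large figures concern covariates the section does not list. This also stands for the arm, which is compared in the primary model with its practice effect. Area deprivation is named under the same objective in section 2.8.2.1, but it is defined by the woman's municipality of residence, so it can differ between women of one practice. Section 2.10.2 analyses it in subgroups handled like the primary endpoint. The stepwise step could be read as admitting further candidates, but no practice-level one is named.

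Third, the protocol gives one intraclass coefficient, no split between practice and GP, and no distribution of practice sizes. In single-GP practices the two levels coincide. The magnitudes are therefore conditional.

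Finally, the wording may be loose. Section 2.10.3 also speaks of physicians as randomised although practices are, the text does not say that physician is the sole random effect, and a GP-level effect is reasonable given the GP/patient pairing in section 2.2. Loose wording would still need correcting, because an analyst following section 2.10.2 literally would omit the practice level.

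**Conclusion.** The point holds as a minor inconsistency in a stated analysis choice. The random effect in section 2.10.2 sits at a different level from the cluster in 2.2, the allocation in 2.5, the primary model in 2.10.1 and the intraclass coefficient in 2.11.1. Correlation between GPs of one practice is not modelled.

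For the listed woman-level predictors, standard errors are about 0 to 5% too small. The true standard error would be roughly 1.2 to 1.4 times the reported one only for a covariate constant within practice, and none is listed. Municipality deprivation, if added, would lie between the two; where is unknown, because the document does not say how far it is shared within a practice.

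These sizes rest on linear-scale approximations rather than a fitted logistic mixed model, and on assumed practice sizes and splits of the intraclass coefficient. The analysis is exploratory, and the non-inferiority conclusion does not depend on it.

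**What to change.** In section 2.10.2, specify a practice random effect with physician nested within practice, so that the model agrees with section 2.10.1 and keeps the GP level. Simply exchanging physician for practice would be second best, because it would drop any extra correlation among women of the same GP. The change matters most if the arm or another covariate shared within practices enters through the stepwise step.

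The cost is one phrase. No new data are needed, since the practice identifier must already exist for randomisation and the GP link is already planned.
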